### Provisions for post-trial care {30}

Enrolled patients are covered by indemnity for non-negligent harm through the standard procedure. Hospices Civils de Lyon have insurance to cover for non-negligent harm associated with the protocol, including additional health care, compensation, or damages.

### Outcomes {12}

The primary outcome is the pain relief measured with a percentage of maximum total pain relief (TOTPAR) over 5 days. TOTPAR is a time-weighted measure of total area under the pain relief curve. This measurement assimilates iterative assessments of a subject’s pain over the duration of the study.

The secondary outcome includes:TOTPAR at day 10, day 20, and day 30 after surgeryThe incidence of severe pain (defined as “severe pain” by the patient)Type, quantity, and doses of taken analgesicsNeuropathic pain prevalence at day 30, detected with DN4 scale [38]The sleep quality measured with Pittsburgh Sleep Quality Index (PSQI) [39] and compared at inclusion day and at the 30th postoperative dayPatients’ perception of postoperative pain management evaluated at with the International Pain Outcome (IPO) questionnaire [40] on day 30 after surgery

### Participant timeline {13}

Patients are followed for 30 days after the discharge from the hospital (Table 1).

**Table 1 Tab1:** Timeline for patients included in the trial

Actions	Days of study										
	–30 to 0	Surgery	1	2	3	4	5	10	20	30	45
Inclusion/exclusion criteria check	X										
Information and written consent signed	X										
Randomization	X										
Neuropathic pain evaluation	X									X	
Sleep Quality Evaluation	X									X	
International Pain Outcome Questionnaire										X	
At-home diary : - Pain relief, % - Medication taken - Side effects		X	X	X	X	X	X	X	X	X	
Recall SMS/email			X				X	X	X	X	
Diary collection											X

*SMS* short message service

### Sample size {14}

In the beginning of our study, we were not able to identify any randomized study of educational intervention with TOTPAR as a primary endpoint. It has been reported, that more than 30% of orthopedic patients suffer from “important” pain (e.g., >6/10) during the first 72 h post-discharge [41, 42]. A 2-point change in the 11-item scale or 30% of the difference in pain intensity measurement is defined as clinically significant [43].

We analyzed the literature, reporting the effect of preoperative education on postoperative orthopedic pain in outpatient settings, and available on the year of the study development. Two studies reported the clinically significant effect from the preoperative education, with calculated OR 1.77 [95%CI 1.12–2.79] to 1.97 [95%CI 1.09–3.57] [44, 45]. However, the quality analysis of these studies demonstrated important heterogeneity, the absence of power calculation, small clinical effects, and design flaws.

As we were not able to find any relevant data for the sample size calculation, we have arbitrarily chosen the OR=2 from the effect of preoperative education, which will produce the decrease of proportion of patients with “important” pain from 30 to 17.6%. Giving this assumption, with the risk alpha of 5% and the power at 80%, allocation 1:1, the calculated sample size was 368 patients. We estimate the loss to follow-up at 10%, therefore the 410 patients will be finally enrolled.

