### Statistical methods

#### Statistical methods for primary and secondary outcomes {20a}

Analyses will be performed on an intention-to-treat basis. All data will be checked for normal distribution, and variables will be presented as mean ± standard deviation (SD) or as the median and interquartile range [IQR] accordingly. Categorical variables will be presented as the number and percentage of the total. To compare the two groups, we will use Fisher’s exact test for qualitative data and the non-parametric Mann-Whitney tests for quantitative variables. A comparison of the two groups at randomization will identify potential bias due to unequal allocation. A multivariate logistic regression analysis will be performed to study conditions independently associated with the response to the intervention and to control potential confounding factors. A 0.05 *p* value will indicate statistical significance. Statistical analyses will be performed using R software (R Foundation for Statistical Computing, Vienna, Austria).

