## Discussion

PELOPS is a randomized controlled trial comparing a structured educational intervention to a control group that receives standard information on pain self-management at home after discharge from orthopedic outpatient surgery. The primary outcome measurement is focused on the time-dependent variable—TOTPAR score as the most sensible, and not on summarizing pain intensity assessment [46], with a clinically significant threshold [43]. A post-discharge burden incurred by patients at home (side effects of treatment, sleep changes, IPO) is assessed as well, because of its importance [42, 47].

Current evidence does not demonstrate a clear effect of preoperative patient education on outpatient pain control. Paucity and methodology weakness (heterogeneous primary outcomes, unclearly defined population, unclearly described intervention) of published studies preclude the inference [12, 13]. Although not blinded (impossible to mask the intervention), this will be the first to our best knowledge randomized study, using meaningful measurement to evaluate the effectiveness of a standardized educational intervention on pain relief at home. Our intervention targets pain relief, independent and universal outcome, and not focused on a specific type of procedure.

Rising popularity of minimally invasive surgeries, thorough selection of patients, and availability of high-quality short-acting anesthesia has led to a dramatic decrease in hospital stay for numerous procedures. The low-risk complications and benefits associated with reduced cost and less hospital stay have driven the growth of the market. Arthroplasty, spine fusion, colorectal resection, and open prostatectomy—procedures associated with important potential for postoperative pain—are more and more performed in ambulatory settings (49). Our study will contribute to the growing evidence base for non-pharmacological pain treatment optimization, as we do not modify surgical analgesics prescriptions. If the study hypothesis is supported, the findings will provide the evidence and the base for educational intervention development in other than orthopedics specialties. As our intervention is not specialist-based, a wide range of clinicians can provide it, individually or in groups, before surgery.

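### The stated 80% power and N = 368 belong to a binary important-pain comparison; the primary TOTPAR comparison has no stated power, difference or SD

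*Protocol article*

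**What the plan says.** Outcomes {12} fixes one primary outcome: "The primary outcome is the pain relief measured with a percentage of maximum total pain relief (TOTPAR) over 5 days". It describes TOTPAR as an area under the pain relief curve, and the data collection section labels pain relief as continuous. Statistical methods {20a} assigns "the non-parametric Mann-Whitney tests for quantitative variables" and Fisher's exact test for qualitative data.

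Sample size {14} works on another scale. It starts from a report that "more than 30% of orthopedic patients suffer from “important” pain (e.g., >6/10) during the first 72 h post-discharge" and says that no trial of an educational intervention with TOTPAR as primary endpoint could be identified. It then explains that "we have arbitrarily chosen the OR=2 from the effect of preoperative education", giving a "decrease of proportion of patients with “important” pain from 30 to 17.6" per cent. From this it concludes that, with "the risk alpha of 5% and the power at 80%, allocation 1:1, the calculated sample size was 368 patients". Allowing 10% loss, 410 are to be enrolled.

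The section also cites a clinically significant change of 2 points on the 11-item scale, or 30% of pain intensity. The Discussion presents TOTPAR "with a clinically significant threshold" and cites the same reference, but no threshold in TOTPAR units appears anywhere in the article.

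**The concern.** The quantity that was sized and the quantity that will be tested differ in four ways.

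| | Sample size calculation | Primary analysis |
|---|---|---|
| Variable | Proportion with important pain | Percent of maximum TOTPAR |
| Scale | Binary | Quantitative |
| Window | First 72 h (from the cited rate) | Five days |
| Test | Two-proportion test (inferred from N) | Mann-Whitney |

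The nearest counterpart of the planning event among the trial's own outcomes is patient-defined severe pain, which is secondary. The clinically significant change concerns pain intensity and does not enter the calculation.

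A reader of the article, or of the final report, will take 80% as the power for the primary outcome. If TOTPAR shows no difference, there is no planned difference to set that result against.

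**Working it through.** **1. Reproducing 368.** Inputs from Sample size {14}: p1 = 0.30, p2 = 0.176, alpha 5%, power 80%, allocation 1:1. Sidedness is not stated; two-sided reproduces the figure and one-sided does not (290). Pooled formula without continuity correction:

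n per arm = [1.960 × √(2 p̄ q̄) + 0.8416 × √(p1q1 + p2q2)]² / (p1 − p2)²

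- p̄ = 0.238, so √(2 × 0.238 × 0.762) = 0.6023
- √(0.210 + 0.1450) = 0.5958
- n = (1.1804 + 0.5015)² / 0.124² = 2.8287 / 0.015376 = 183.97

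That is 184 per arm and 368 in total, as stated. Loss: 184/0.9 = 204.4, so 205 per arm and 410.

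**2. Same calculation with p2 unrounded.** OR 2 from 30% gives odds (0.30/0.70)/2 = 0.2143, so p2 = 0.17647. The formula then gives 186 per arm and 372 in total; 186/0.9 = 206.7, so 207 per arm and 414. The abstract's 414, and the 186 target in the missing-data section {20c} if read as per arm, fit this variant. Sample size {14} uses the other.

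**3. The binary comparison under the plan's own test.** Exact enumeration at 184 per arm, 30% vs 17.6%: uncorrected chi-square 80.3%, Fisher's exact test 76.8%.

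**4. What 184 per arm gives for TOTPAR.** Two-sided 5%, 80% power:

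- Comparison of means: d = (1.960 + 0.842) × √(2/184) = 0.292
- Mann-Whitney, normal shift (relative efficiency 3/π = 0.955): 0.292/√0.955 = 0.299
- Mann-Whitney at its lower efficiency bound for shift alternatives (0.864): 0.292/√0.864 = 0.314
- Probability of superiority at d = 0.299: Φ(0.299/√2) = 0.584

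Mann-Whitney power is 47% at d = 0.20, 65% at 0.25 and 80% at 0.30.

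**5. In TOTPAR points.** The article gives no SD, so the SDs below, and the 5- and 10-point differences, are assumptions. Mann-Whitney, normal shift, 184 per arm:

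| Assumed SD | Difference with 80% power | Power for 5 points | Power for 10 points |
|---|---|---|---|
| 20 | 6.0 | 65% | 99.7% |
| 25 | 7.5 | 47% | 96% |
| 30 | 9.0 | 34.5% | 88% |
| 35 | 10.5 | 27% | 76% |
| 40 | 12.0 | 21.5% | 65% |

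Over this grid, power runs from about 22% to above 99%. The document does not narrow it further.

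**The case against.** The authors are open about what they did: they found no usable TOTPAR data, took a neighbouring endpoint, and called the effect arbitrary. The sum is right. An OR of 2 carried over to a logistic latent scale is a standardised difference of ln 2/1.814 = 0.38, for which Mann-Whitney has about 95% power at 184 per arm. A positive result needs no planned difference to be interpretable, and a null one can be read from its confidence interval. The full French protocol, which is not shown, may say more.

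Most of this stands, and it limits the point. Disclosing a substitute endpoint still does not carry its power across. The 0.38 conversion assumes that an odds ratio for exceeding a pain threshold in 72 hours acts equally across the whole five-day TOTPAR distribution, and nothing in the article supports that. Nor is this a detail left to a fuller document: the article gives a complete justification with alpha, power, effect and N, attached to an endpoint that is not primary.

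A reader might also infer that the planning event is not recorded in the diary, because no 0–10 intensity score is listed there. The documents do not support that. The data collection section {18a} includes a binary severe-pain item that patients judge for themselves, and the value above 6/10 in the sample size section is only an example. Two smaller facts remain: no 0–10 score is listed as a diary item, and the diary row of Table 1 omits the severe-pain item that {18a} includes.

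The Fisher shortfall is a side matter. It concerns a secondary outcome for which no power is claimed.

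**Conclusion.** The point holds as a mismatch between endpoint and sample size. The 80% and the 368 are correct for 30% vs 17.6% with important pain. They do not describe the primary TOTPAR comparison, for which the article states no power, difference or SD.

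Two stronger readings are not supported. There is no arithmetic error in 368, which reproduces exactly. The trial is also not shown to be underpowered: 184 evaluable patients per arm detect a standardised difference of about 0.30 with 80% power (0.29 to 0.31 over the efficiencies considered). Whether that is small enough to be useful depends on a TOTPAR SD and a relevant difference that the article does not give.

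The 0.30 rests on a normal shift. Percent of maximum TOTPAR is bounded, and the missing-data section {20c} sets it to 100% from the next blank page when a completed diary has no pain relief entries after day three. Ceiling values and ties could make the approximation less accurate.

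**What to change.** Keep N and rewrite the paragraph in three parts.

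1. **Secondary outcome.** Label the 30% to 17.6% calculation as applying to the severe-pain outcome, and state its window, since the planning rate covers 72 h and the abstract's severe-pain outcome covers 30 days. Note that power is about 77% with the planned Fisher's exact test.
2. **Primary outcome.** Suggested wording: *About 184 evaluable patients per arm give 80% power, two-sided 5%, for a standardised difference of about 0.30 in percent of maximum TOTPAR (probability of superiority about 0.58) by Mann-Whitney, under a normal-shift approximation.* Present this as what the fixed N can detect, not as a clinically derived target. Convert it to TOTPAR points with one SD over both arms combined, calculated with the arm variable removed, from diaries already returned. The article reports 256 recruited; the number returned is not given. Ignoring arm inflates the SD only slightly: at d = 0.30 by √(1 + 0.30²/4) = 1.011. Use the same data to check for ceiling values and ties arising from the 100% rule.
3. **Numbers.** Choose one set, 184 per arm/368/410 or 186 per arm/372/414, and use it in the abstract, Sample size {14} and the missing-data section {20c}, saying whether the target is per arm or in total.

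The cost is one paragraph, one SD calculation without arm labels, and no additional patients beyond whichever of the two enrolment totals is kept. Because the edit touches stated sample sizes, it probably needs the formal amendment and notification that the protocol requires for such changes.

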### Recruitment {15}

Our institution performs at least 50 orthopedic outpatient procedures monthly. Anesthesiologists’ team (6 practitioners) systematically evaluates all patients at least 48 h before the planned surgery. As we do not expect to recruit every patient, we would need at least 48 months for the inclusion target accrual.

### Assignment of interventions: allocation

#### Sequence generation {16a}

Enrolled patients will be randomly assigned to a control or interventional group with a 1:1 allocation using Ennov Clinical® software (Paris, France) with an embedded IWRS (Interactive Web Response System) randomization system. Patients will be stratified by the type of surgery (knee, hip, or shoulder isolated arthroscopy, MPFL, Kenneth Jones or Hamstring anterior cruciate ligaments repair, posterior cruciate ligaments repair, Latarjet open shoulder procedure, and video-assisted rotator cuff repair) and type of anesthesia (spinal, general, combined general and regional anesthesia). The configuration of the randomization and the implementation of the randomization list in the software were made by the statistician who is not involved in the process of patient inclusion and randomization. The list was created with variable block size using nQuery Advisor®, 7.0 (Statistical Solutions Ltd, Cork, Ireland). No one, except the statistician, has access to the randomization list.

#### Concealment mechanism {16b}

The result of randomization will be available after obtaining the patient’s consent, and before study group assignment, using an online, central randomization service IRWS. Allocation concealment will be ensured, because the IRWS will not issue the group assignment until the patient has been recruited into the trial.

#### Implementation {16c}

Recruiting physician will use IRWS of the Ennov Clinical® software to receive allocation instructions and will give the information about allocation to the patient.

There will be no other changes in anesthesia protocol or postoperative care protocol, the same standard at-home analgesics prescription is provided for all patients at discharge by surgeons.

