### Who will take informed consent? {26a}

Patients will be recruited during the pre-anesthesia visit by a physician anesthesiologist. After meeting inclusion criteria, each patient will be orally informed about the study protocol first. Agreed patients will sign a written consent form and will be randomized to receive either standard information on postoperative pain management or structured education intervention. A physician anesthesiologist, performing pre-anesthesia evaluation and patients’ inclusion, collects the written consent.

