## Interventions

### Explanation for the choice of comparators {6b}

#### Standard pain information

The standard recommendation on postoperative pain management for outpatient procedures is based on the recommendation of the French National Agency for Medication and Medical Products Safety (Agence nationale de sécurité du médicament et des produits de santé –ANSM) and the French Society of Anesthesia (SFAR), available through the site of the French national system of health insurance [21, 22].

These recommendations include an example of 11-item numeric pain scale (0 – no pain, 10 – worst imaginable pain) divided into three levels—light to moderate (0 to 4, light orange code), moderate to intense (4 to 7, orange code), and intense to very intense (7 to 10, dark orange code).

The following narration is used:Your pain treatment has to be taken starting your return home. To evaluate your pain, use the digital scale from 0 to 10. In a case of light to moderate pain (0-4), you should take paracetamol. For moderate to intense pain (4-7), you should take anti-inflammatory or opioid-containing drugs.The treatment is systematic during first 3 days. Prescribed dosage should be respected.

All patients were free to ask any additional questions about pain management at home.

At the end of visit, a diary for data collection is given to a patient, containing the comparator standard pain scale on the first page, and the narration on the second page.

All parents (both from the control and intervention arms) receive a standardized analgesics prescription for at-home pain management, including acetaminophen, ketoprophen (non-steroid anti-inflammatory drug), weak opioid formulation (based on opium), and proton pump inhibitors (gastric protector).

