### Intervention description {11a}

The structured education intervention is derived from the well-known and validated 11-items pain intensity scale. The intervention allows the anchoring of each level of pain scale on the individual patient’s experience. In the case of outpatient surgery, patients are empowered to act on medical (post-surgical pain, functional disability) and social constraints (return home, autonomy, home burden, family, no immediate access to a healthcare provider). Patients receive oral, visual (interaction with a clinician), and material support (diary with scale and script), delivered by a clinician, in a standardized manner.

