### Assignment of interventions: blinding

#### Who will be blinded {17a}

Due to the nature of the intervention, the allocation cannot be masked neither for participants nor for physicians or data managers

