### Data collection and management

#### Plans for assessment and collection of outcomes {18a}

A dedicated electronic case report form (e-CRF) within Ennov Clinical® software was created and managed by Clinical Research Department, Hospices Civils de Lyon. The following data are collected upon inclusion: demographics, type of surgery, type of anesthesia, assessment of neuropathic pain with DN4, and assessment of the sleep quality with PSQI. After the discharge, patients fill in the dedicated diary. The prevalence of severe pain (which patients deem to be important) (binary), pain relief (continuous), painkiller administration (binary), and side effects from painkiller (binary) are collected in a time-dependent manner with 30 min grid over 24 h. On day 30, patients fill in the assessment of neuropathic pain with DN4, assessment of the sleep quality with PSQI, and the International Pain Outcome questionnaire (multiple binary, categorical and continuous variables). After the diary completion, patients were asked to send the collected data to the investigators.

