#### Adverse event reporting and harms {22}

The nature of the study (education intervention) is not intended to produce any harm. However, at the last visit, any potential adverse effect will be collected by the responsible surgeon.

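### The statement that no physician can be masked is broader than its reason supports, and leaves the adverse effects collected by the surgeon open to avoidable ascertainment bias

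*Protocol article*

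**What the plan says.** All references are to the protocol article.

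- **Masking.** Section {17a} states that "the allocation cannot be masked neither for participants nor for physicians or data managers" and gives the nature of the intervention as the reason. Section {17b} adds that there is no blinding.
- **Who holds the allocation.** Section {26a}: "Patients will be recruited during the pre-anesthesia visit by a physician anesthesiologist". Section {16c} has the recruiting physician use the web system "to receive allocation instructions and will give the information about allocation to the patient".
- **Who educates.** Section {11a} says the material is "delivered by a clinician, in a standardized manner". The specialty is not named.
- **What surgeons do.** Section {16c}: "the same standard at-home analgesics prescription is provided for all patients at discharge by surgeons". Section {22}: "at the last visit, any potential adverse effect will be collected by the responsible surgeon".
- **Where the diary goes.** The subsections on standard pain information and on delivery of the education put the arm's own pain scale on the first page of the diary and the arm's narration on the second. Section {11c} expects patients to bring the completed diary to the scheduled surgical visit on day 45, or to post it.
- **Analgesic side effects.** These are recorded separately by the patient: section {18a} says that "side effects from painkiller (binary) are collected in a time-dependent manner with 30 min grid over 24 h".

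**The concern.** A reason that holds for some people has been applied to all physicians. An educational talk cannot be hidden from the person who receives it or the person who gives it. It can be kept, at least in part, from a surgeon in another department who was not present and does not need to know the arm.

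This matters because the surgeon is the assessor in the only adverse-effect route that section {22} describes. That section gives no structured method of enquiry. If the surgeon knows the arm, how the question is put, how far it is pursued and which complaints are written down can all differ between arms. Such a difference would look like an effect of the education on harms and could not be removed in the analysis. The trial hypothesis includes fewer analgesic-related side effects, so an assessor who knows the arm also knows which direction is expected.

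**Working it through.** No arithmetic bears on this point. The check is to set the sections side by side.

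**1. Whom does the stated reason cover?** The nature of the intervention explains why the patient and the person delivering the education cannot be masked. It also explains why anyone who handles an open diary cannot be, since the first two pages show the arm.

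**2. Are surgeons in one of those groups?**
- Recruitment and consent: an anaesthesiologist, at the pre-anaesthesia visit ({26a}).
- Receipt and disclosure of the allocation: the recruiting physician ({16c}), hence the same anaesthesiologist.
- Setting: a team of six anaesthesiologists evaluates all patients at least 48 h before surgery ({15}).
- Education and diary: the diary is handed over at the end of the visit in both arms.
- Delivery: a clinician of unnamed specialty ({11a}).

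Every section that names a role points to the anaesthesiologist. That surgeons take no part in the education is an inference from these sections. The article does not say so outright.

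**3. Which surgical task could be affected?**

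| Task or measure | Who acts or reports | Exposed to surgeon's knowledge of the arm? |
|---|---|---|
| Discharge prescription | Surgeon, same standard order in both arms ({16c}) | Little: no discretion is stated |
| Additional medication | Allowed to the patient and traced in the diary ({11d}) | Little: the patient knows the arm anyway |
| Pain relief, severe pain, analgesic intake, analgesic side effects | Patient, in the diary ({18a}) | No |
| Neuropathic pain, sleep and pain-perception questionnaires at day 30 | Patient ({18a}) | No |
| Adverse effects at the last visit | Responsible surgeon ({22}) | Yes |

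**4. Is there a route by which the surgeon learns the arm?** Yes, and the protocol creates it. The diary identifies the arm on opening ({6b}, {11a}) and is expected at the day-45 surgical visit ({11c}; Table 1 places diary collection there). Section {22} does not date the last visit. Day 45 is the only visit after discharge that the article describes, so I take the two to be the same.

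**5. How many patients could a change still cover?** The trial status section reports 256 recruited at manuscript revision. The planned total is 410 in section {14} and 414 in the abstract, so 410 − 256 = 154 or 414 − 256 = 158 were still to be enrolled. Patients already enrolled but not yet seen at the last visit would add to this. Their number is not given.

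**The case against.** The strongest reply is that this is an openly unblinded trial in which no listed outcome is assessed by a surgeon. The side effects of medication named among the objectives are the patient's own diary entries, and the surgeon's enquiry at the last visit is a general safety check that does not appear among the outcomes in section {12}. This stands, and it is why the point is minor.

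The reply goes on that surgeon masking would be fragile: patients are told their arm and may mention it. No section says that surgeons are told the arm, that it is entered in the surgical chart, or that the surgeon is the one who receives the diary; research associates transcribe it ({19}). This stands in part. Fragility limits what masking can achieve, but partial masking with disclosures recorded is better than a blanket statement that it cannot be done. The diary route is one the protocol itself can close.

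A reader might infer something stronger: that unmasked surgeons could treat the arms differently at discharge and so distort the primary comparison of pain relief. The article does not support that. The subsection on standard pain information says patients in both arms "receive a standardized analgesics prescription for at-home pain management", and section {16c} rules out other changes in anaesthesia or postoperative care. The sentence on the surgeons' prescription is therefore a safeguard. Additional treatment is left to patients, who cannot be masked, so masking surgeons would not close that route.

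**Conclusion.** The concern holds in a narrow form. Section {17a} overstates what the nature of the intervention makes impossible, and as a result the adverse effects collected by the surgeon are open to ascertainment bias that could be reduced at little cost.

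Severity is minor. The article offers no figures from which to estimate the bias. Its reach is one item outside the listed outcomes. The total pain relief score and the patient-reported secondary outcomes are not affected, and any effect on co-treatment is minor because the prescription is the same in both arms.

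The conclusion rests on two assumptions: that surgeons do not deliver the education, and that the last visit in section {22} is the day-45 surgical visit. If surgeons do deliver it, the statement in {17a} would be justified for those surgeons, and the remedy would be to have someone else collect adverse effects.

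**What to change.** 1. **Section {17a}.** Limit the no-masking statement to participants, those who deliver the education, and those who handle the diaries. State that the surgeon who collects adverse effects is not told the arm. In {11a}, name who delivers the education.
2. **Records.** Do not write the arm in surgical or discharge papers.
3. **Sections {11c} and {18b}.** Have every diary, posted or brought on day 45, returned in the sealed prepaid envelope to research staff and not to the surgeon. The envelopes are already part of the plan.
4. **Section {22}.** Have the surgeon record adverse effects on one fixed form used in both arms, without being told the arm, and note on it whether the patient disclosed it.
5. **Reporting.** Make the change through the amendment route in section {25}. Report its date and how many patients had already attended the last visit.

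The cost is an amendment, a working instruction and a short form, with no extra staff. Masking will be partial, because some patients will reveal their arm. It will also apply only to patients not yet seen at the last visit, so adverse effects will have been collected under two regimes. Describing those before and after the change separately would make that visible.
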